**Fig 2 pone.0256043.g002:**
[figure not shown]
Baseline screening algorithm.

*Follow-up*. All participants with no evidence of TB at baseline will be contacted by phone approximately four-monthly to ask whether they have been diagnosed with TB in the interim. Also, to enable the study team to capture the sputum sample and obtain a culture at the time of diagnosis, household contacts will be given a referral card with the study contact details they can show to any CHC or hospital should they present with any TB symptoms or undergo any TB related diagnostic tests. At 12 months a repeat in-person symptom screen will be done (Fig 3). If an individual within a household leaves the neighbourhood area and cannot be followed-up, the approximate date they left will be ascertained from other household members. If a whole household leaves the area before the 12-month follow-up and are unable to be contacted, an approximate date will be confirmed from neighbours.

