### Outcome measures and statistical analysis

We will categorize TB for Index and household/neighbourhood contacts into four categories: definite TB, probable TB, possible TB, and not TB. Subjects are categorised as definite TB if their *Mtb* culture or Xpert MTB/RIF positive; probable TB if they have TB symptoms, chest x-ray suggestive of TB, and AFB smear-positive but culture negative/not done; possible TB if they have TB symptoms and/or chest x-ray suggestive of TB but all bacteriology examinations negative/not done; and not TB if there was no evidence of TB on a symptom review or investigations. Chest x-rays will be classified as normal, suggestive active TB, suggestive inactive TB, or abnormal not TB based on the radiology report.

The key outcomes of this study are to estimate the TB prevalence and incidence in neighbourhoods around known TB cases, compared to households of known TB cases. TB prevalence defined as the number, percent and 95% confidence intervals (CI) of positive TB cases, according to each TB definition (definite, probable, possible), will be estimated. These proportions will be compared between households, neighbourhoods, and estimates from the Indonesian National Prevalence Survey for Java/Bali. TB incidence defined as incidence rates and 95% CI of positive TB cases according to each TB definition (definite, probable, possible), will be calculated per 1000 person-days. Person-days will be calculated as the days from the date of baseline examination to either: a) the date of TB diagnosis, b) date of death (if died) as reported by household member, c) date of 12-month follow-up examination, or d) date left the neighbourhood area for any household member who has left the area before the 12-month follow-up.

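### Leavers' person-days run to a proxy-reported departure date rather than to the last date TB status was known, so unobserved time enters the incidence denominator

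*Protocol article*

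**What the plan says.** TB incidence in neighbourhoods and households is a key outcome. The protocol article, Outcome measures and statistical analysis, defines the denominator as follows:

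- Start, and first end point: "Person-days will be calculated as the days from the date of baseline examination to either: a) the date of TB diagnosis".
- Second end point: "b) date of death (if died) as reported by household member".
- Third end point: "c) date of 12-month follow-up examination".
- Fourth end point, d): "date left the neighbourhood area for any household member who has left the area before the 12-month follow-up".

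The Follow-up paragraph (under Prospective cohort study) describes how TB status becomes known. Participants without TB at baseline "will be contacted by phone approximately four-monthly to ask whether they have been diagnosed with TB in the interim". A referral card lets a clinic or hospital alert the study to a diagnosis between calls. "At 12 months a repeat in-person symptom screen will be done".

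The same paragraph covers departures. If one person "leaves the neighbourhood area and cannot be followed-up, the approximate date they left will be ascertained from other household members". If a whole household has gone and is out of reach, "an approximate date will be confirmed from neighbours". In both cases the information sought is a date. The article does not say that the informant is asked about TB.

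**The concern.** An incidence rate is unbiased only if a case occurring on any counted day could also have been counted. End point d) does not secure this. The proxy date is sought for people the study can no longer reach, and they are the people whose status since the last successful call is least likely to be known. Days between that call and the reported departure go into the denominator, while a case in those days may never reach the numerator. For leavers the effect on the rate can only be downward.

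The list of end points also has a gap. A participant who is alive, undiagnosed and still living in the area, but refuses or cannot be found at 12 months, meets none of a) to d). The Discussion expects that COVID-19 may hinder follow-up, so this group is foreseeable.

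At stake are the level of a key outcome and, if leaving or phone contact differs between the groups, the household–neighbourhood comparison.

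**Working it through.** **Plan's own figure.** There is none to reproduce. The Sample size section covers prevalence and genomic relatedness, not incidence, and no loss rate is stated.

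**Inputs from the protocol article**
- Calls about every four months, taken as days 122 and 243; screen at 12 months, taken as day 365 (Follow-up).
- About 4500 neighbourhood and 1000 household participants (Abstract).
- Feasibility rates of 675 (neighbouring households) and 649 (household contacts) per 100,000 per year (Introduction).

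**Assumptions (not in the article)**
- Constant hazard and non-informative loss.
- A fraction L leaves and cannot be reached, with L from 5% to 30%. Departure dates are uniform over 365 days.
- No case after the last contact is captured.

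**Step 1: unobserved gap per leaver.** Mean time to departure is 365/2 = 182.5 days. If every call before departure was answered, the last contact is day 0, 122 or 243, for departures in the first, second or last third of the year. Its mean is (0×122 + 122×121 + 243×122)/365 = 121.7 days. The mean gap is 182.5 − 121.7 = 60.8 days, about two months.

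**Step 2: estimated rate divided by true rate.** Cases are proportional to observed time; the denominator is counted time.

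- All earlier calls answered: [365(1−L) + 121.7L] / [365(1−L) + 182.5L]
- No call answered, so only baseline is known: 365(1−L) / [365(1−L) + 182.5L]

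At L = 0.10: (328.5 + 12.17)/(328.5 + 18.25) = 340.67/346.75 = 0.983, and 328.5/346.75 = 0.947.

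At L = 0.20: (292 + 24.33)/(292 + 36.5) = 316.33/328.5 = 0.963, and 292/328.5 = 0.889.

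| Leavers (L) | Calls answered: ratio | A true 675 becomes | No call answered: ratio | A true 675 becomes |
|---|---|---|---|---|
| 5% | 0.992 | 669 | 0.974 | 658 |
| 10% | 0.983 | 663 | 0.947 | 639 |
| 20% | 0.963 | 650 | 0.889 | 600 |
| 30% | 0.941 | 635 | 0.824 | 556 |

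Ending person-time at the last contact with known status gives a ratio of 1.00 under the same assumptions.

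**Step 3: comparison with sampling error.** Expected cases with full follow-up are 4500 × 0.00675 = 30.4 and 1000 × 0.00649 = 6.5. The Poisson relative standard errors are 1/√30.4 = 18% and 1/√6.5 = 39%.

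**Step 4: residents lost to contact.** The article fixes no handling for them. Let R be the fraction lost, with last contact equally likely at day 0, 122 or 243 (mean 121.7). For R from 5% to 30%:

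- Run to a nominal 12 months, [365(1−R) + 121.7R]/365: 0.967 to 0.800 (downward).
- Excluded entirely, under non-informative loss: 1.00.
- Phone-reported cases kept but the other person-time dropped, [365(1−R) + 121.7R]/[365(1−R)]: 1.018 to 1.143 (upward).

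**Step 5: a trap in the obvious repair.** Suppose non-cases are cut at the last call while referral-card cases after that call still count. If the card captured every gap case, the ratio would be 346.75/340.67 = 1.018 at L = 0.10 and 328.5/316.33 = 1.038 at L = 0.20. The repair would then bias the rate upward by about as much as the present rule can bias it downward.

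**The case against.** Four arguments on the other side deserve weight.

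**Ascertainment between calls is not nil.** The referral card can bring in a diagnosis, and remaining household members may know of one. A leaver who still answers the phone can report status directly. This stands as mitigation. The figures for leavers in steps 1 and 2 assume that no gap case is captured; if half were, the 2–4% would become about 1–2%. It does not remove the problem, because the proxy date is sought where contact has failed and the article asks the proxy only for a date.

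**The bias is small.** At 10–20% leaving with calls answered it is 2–4%, against relative standard errors of 18% and 39%. This stands. However, the bias does not shrink with sample size and the confidence interval does not reflect it.

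**The lost-resident rule may be in a fuller document.** A condensed article commonly leaves such a rule to the full protocol or analysis plan, so its absence here is not the basis of this point. The leaver rule is stated outright and is the firm part.

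**Stronger readings go too far.** A reader might infer that all the incidence rates are biased downward, lost residents included. The article does not support that: with no handling fixed, the direction for lost residents can be downward, nil or upward. Nor does it follow that dropping them must be wrong; under non-informative loss it is unbiased. A reader might also assume an average gap of up to four months. Four months is roughly the maximum when calls are answered, and the average is about two. Finally, nothing in the article shows that neighbours are harder to reach than household contacts, so no direction can be given for the comparison between them.

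**Conclusion.** The concern holds for leavers. The stated rule lets time without known TB status into the denominator, and the resulting bias is downward. At an assumed 10–20% leaving it is about 2–4% if earlier calls were answered and 5–11% if none were. These sizes rest on assumed loss, uniform departure, constant hazard, non-informative loss and no capture of gap cases. The effect is minor beside the expected sampling error, but it is systematic and easily avoided.

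For residents not examined at 12 months, the only supportable statement is that none of the four end points applies and that the direction of bias depends on a handling this article does not fix. The three plausible handlings give three different answers, which is reason to settle one in advance.

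**What to change.** - When a household member or neighbour gives a departure date, also ask whether TB was diagnosed up to that date. Use the departure date only if status was confirmed. Otherwise end person-time at the last call or visit at which TB status was ascertained.
- Apply the same last-known-status rule to residents not examined at 12 months, unless a fuller document already sets a rule; in that case, cite it.
- Count cases and person-time over the same window. A case that reaches the study only through the referral card after a participant's last contact should not enter the main rate while non-cases are censored at that contact.
- Add two sensitivity analyses: one using the departure date as now written, and one for participants without the 12-month screen. For the latter, TB status rests on self-report or passive detection, which is weaker than the in-person screen, so censoring at last known status is not a full remedy.

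The cost is a few sentences in the plan and one more question to the informant. Call dates already arise from the four-monthly contacts. Person-time falls slightly, and a few cases may move from the main rate to the sensitivity analysis, which matters a little with only about 6.5 household cases expected.

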### Data handling

Information collected during interviews will be recorded on an electronic case report form (CRF) or paper-based CRF in case of internet connection problem. Standard operating procedures on interview procedure and data entry will provide the necessary guidelines for research staff. A monthly check will be done for data completeness and accuracy. All databases and data collection tablets will be password protected.

### Ethical considerations

#### Research ethics approval

The protocol and consent forms have been reviewed and approved by the University of Otago Human Ethics Committee (reference number H20-054) on 28 May 2020, translated into Bahasa Indonesia and approved by the Universitas Padjadjaran Health Research Committee (reference number 1129/UN6.KEP/EC/2020) on 3 December 2020.

#### Confidentiality

Participants will be assured of their confidentiality, that no identifiable information will be shared with anyone outside of the research team, and that they can refuse to answer any question if they feel uncomfortable. Each study participant will be given a unique study identification number that will be on all study documentation and in the database. The names and contact details of participants will be required in order to contact them for the 12-month follow-up interview, but these details will only be known to the relevant research nurse. The database with identifiable names and addresses will be separate from the main database that is available to researchers for the analysis. Signed consent forms will be stored in a locked cabinet.

#### Potential risks and benefits

TB continues to be a stigmatising disease and therefore Index cases may feel exposed and not wish to be identified. This risk will be minimised by the Index case first being asked by CHC staff if they are willing for their name and contact details to be given to the research staff. At the visit, Index cases will be asked for their consent to screen their household members, as well as neighbouring household members. They will be given reassurance that their identity and their TB status will not be revealed to neighbouring households and staff will be trained in issues of confidentiality and follow standard operating procedures. All participants will be informed about the study and given the opportunity to discuss it with their families before giving their consent. COVID-19 continues to be prevalent in Indonesia, therefore strict safety protocols will be adhered to by the research team to prevent the risk of transmission.

## Discussion

The World Health Organization (WHO) 2020 Global TB Report showed Indonesia had the second highest TB incidence in absolute numbers [1]. In 2015, the National TB Program budget was estimated to be 133 million US dollars, much of which is unfunded [15]. This study will confirm whether neighbourhoods in the vicinity of routinely diagnosed TB index cases constitute a high-risk sub-population that may warrant active intervention to enhance TB control. Evidence provided will be crucial for the Indonesian TB Control Program in scaling up efforts towards the elimination of TB in a targeted and cost-effective way.

The combination of high precision genotyping, expanded social network questionnaires, and network analyses provides the opportunity to explore *Mtb* transmission. Genomic and social network analyses will provide important information to guide the design of possible interventions that may include active case finding, preventive treatment, and/or enhanced infection control measures in specific locations. For example, if ‘recent’ transmission of *Mtb* from index case households to neighbourhoods is indicated as explaining a large component of high neighbourhood prevalence, an intensive intervention of active case finding for early diagnosis and treatment would be warranted. If transmission ‘hotspots’ within the neighbourhoods can be identified, infection control measures could be considered. If high prevalence and incidence of TB is confirmed but there is a relatively low rate of genomic match within neighbourhoods, it may be that socioeconomic factors that promote reactivation are predominant. An intervention of screening for latent TB infection and initiation of preventive treatment to reduce the possibility of reactivation could be considered, or the focus could be on socioeconomic factors themselves, as suggested by WHO as part of the global strategy to End TB [23].

The proportion of TB cases that can be included in the analysis will be crucial to the ability to interpret these data. As COVID-19 continues to be prevalent in Indonesia, it is possible that recruitment and follow-up will be hindered with fewer than expected numbers being included in the study. This information will be closely monitored and every attempt made to follow-up participants through regular phone contact.

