## Introduction

Tuberculosis (TB) remains a leading cause of infection globally, with an estimated 10 million new cases of disease and 1.2 million deaths from TB in 2019 [1]. To eliminate TB, we need to identify target populations most at risk so that enhanced intervention can drive the incidence of TB down across the wider population. Many attempts to intensify TB control efforts have focused on TB households [2–4]. However, we now know that in most high burden settings, the majority of *Mycobacterium tuberculosis (Mtb)* transmission occurs in the community where there are vastly greater numbers of human encounters [5] that often share socio-economic risk factors that are correlated with TB [6, 7]. In a feasibility study in Bandung, Indonesia [8] we followed individual TB patients back to their communities. We found an incidence rate of self-reported TB of 649 per 100,000/year in TB household contacts, 675 in neighbouring households, and 325 in randomly selected neighbourhoods [8].

TB disease occurs through two distinct mechanisms (primary progression and reactivation) that require different interventions. Soon after exposure to *Mtb*, a small proportion of people develop TB disease (primary progression) and approximately 50% of them are latently infected but remain well. Of these latently infected people, 5% develop TB disease during their lifetime (reactivation) [9–11]. Early diagnosis and six months of multi-drug treatment of TB disease reduces transmission to case contacts, and preventive treatment of latent TB for as little as three months reduces reactivation in infected contacts by up to 90% [12, 13]. Both strategies are essential for TB elimination [14]. If neighbourhoods around TB cases have high rates of TB, then this is likely to be due to a particular mix of primary progression and reactivation disease.

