#### 1) Prospective cohort study

*Study participation and recruitment*. From 250 bacteriologically-proven TB patients (Index case) living within one of the six selected CHC areas of Bandung City (as described above), we will conduct active case finding among household contacts (approximately four people per household) and neighbourhood members. Trained research staff will interview all persons aged 10 years and above living in the same household as the Index case, as well as all those living in the five houses closest to the Index case. We will record all subjects in the target households and assess their eligibility. We will not exclude any person with extra-pulmonary TB or being re-treated for TB for screening or follow-up. We will exclude any person in a household who normally lives at another location, or children under the age of 10 years.

The TB nurse in each recruitment site (CHC or hospital) will identify potential Index cases, ensure they are resident in the selected area and seek consent for their contact details to be forwarded for the study. Research staff will then contact consenting Index cases to arrange a time to visit them and their household when most household members are likely to be present. At the visit, further information will be provided and written informed consent obtained. The Index case will also be informed that we wish to contact neighbourhood households and their consent sought before proceeding. Research staff will identify five houses that are the closest in proximity from the Index case house. Within each identified neighbourhood household, the same procedure of informed consent will be followed. The research staff will be instructed not to reveal the identity of the Index case. Consent for any household members aged between 10 and 18 years will be sought from their parent or guardian.

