#### Genomic relatedness

We expect a maximum of 10% (95% CI 6.3–13.7%) of 250 community diagnosed Index TB cases will have an *Mtb* isolate that is genomically ‘identical’ to another Index case, compared to approximately 60% of Index TB case/household contact TB case pairs. Percentages for Index case/neighbourhood case pairs will lie between these values. Assuming we identify 35 culture-positive cases in contacts in 250 households and 75 culture-positive cases in neighbourhoods, we will have >95% power to detect significant differences (p = 0.05 level of significance), in percent genomically ‘identical’, for comparisons between community and Index TB case/household TB case pairs and between community and Index TB case/neighbourhood case pairs. We will also have over 80% power to detect a significant difference for a household versus neighbourhood comparison, if 60% or more of Index case/household case pairs are genomically ‘identical’ and 30% or less of Index case/neighbourhood case pairs are genomically ‘identical’.

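### A low genomic match in neighbourhoods cannot by itself separate reactivation from recent infection by an unsequenced source, and the Discussion offers only the first reading

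*Protocol article*

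**What the plan says.** The Discussion links genomic results to possible programme responses. If recent spread from Index households to neighbours explains much of a high neighbourhood prevalence, "an intensive intervention of active case finding for early diagnosis and treatment would be warranted". For high prevalence and incidence with few links, the sentence runs: "relatively low rate of genomic match within neighbourhoods, it may be that socioeconomic factors that promote reactivation are predominant". The response attached to that case is: "An intervention of screening for latent TB infection and initiation of preventive treatment to reduce the possibility of reactivation could be considered", or a focus on socioeconomic factors.

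The set of people who can be sequenced is fixed in Methods. Recruitment starts "From 250 bacteriologically-proven TB patients (Index case) living within one of the six selected CHC areas of Bandung City" and takes in the Index household and "all those living in the five houses closest to the Index case", from age 10 upwards. Under 'Whole-genome sequencing and social network analysis', sequencing is done on cultured isolates from Index cases and from contacts diagnosed with TB. The expected yield, under 'Genomic relatedness', is: "Assuming we identify 35 culture-positive cases in contacts in 250 households and 75 culture-positive cases in neighbourhoods".

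Two other statements bear on the point. The Introduction says that in most high-burden settings most transmission takes place in the wider community. The Discussion also warns: "The proportion of TB cases that can be included in the analysis will be crucial to the ability to interpret these data". The sentences after that warning concern only COVID-19, recruitment and follow-up.

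**The concern.** A genomic match can be seen only if the source, or another member of the same transmission chain, is also sequenced. Reactivation of an old infection gives a non-match. So does recent infection from a person outside the sequenced set. The Introduction's own premise makes the second route an expected one.

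The error has a direction. Every unsequenced source lowers the observed match, and the Discussion reads a lower match as reactivation. The study exists to tell the TB programme what kind of action neighbourhoods need, and the two readings lead to different actions.

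A related weakness lies in the high-match branch, which speaks of spread outward from Index households. Pairwise SNP distance is symmetric. A match fits equally well with the neighbour, or a shared third person, as the source.

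**Working it through.** **1. The plan's own figures.** These reproduce.
- Interval for 10% of 250: 0.10 ± 1.96 × √(0.10 × 0.90 / 250) = 0.10 ± 0.037, or 6.3% to 13.7%, as stated.
- Power, two-sided 0.05, from Φ[(|p1 − p2| − 1.96 × √(p̄(1 − p̄)(1/n1 + 1/n2))) / √(p1(1 − p1)/n1 + p2(1 − p2)/n2)]:
  - household 60% of 35 against community 10% of 250: above 99.9%
  - neighbourhood 30% of 75 against community 10% of 250: 97.4%
  - household 60% of 35 against neighbourhood 30% of 75: 85.5% (81.9% by Fisher's exact test)

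The sample-size statements are therefore not in question. The issue is what a low match means.

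**2. Share of possible sources sequenced (f).** Inputs: 2.4 million inhabitants, 80 CHCs, 647 per 100,000 and 2200 notifications a year (Introduction); 0.5%, 95% CI 0.4 to 0.6% (Sample size, prevalence); 250, 35 and 75 cases (Genomic relatedness). Equal catchments are my assumption.
- Sequenced, if all yield an isolate: 250 + 35 + 75 = 360.
- Population of six areas: 2.4 million × 6/80 = 180,000.
- Prevalent cases: 180,000 × 0.00647 = 1165, or 180,000 × 0.005 = 900 (720 to 1080 over the survey interval).
- f = 360/1165 = 31%, or 360/900 = 40% (33% to 50% over the survey interval).
- Narrower comparator: CHC smear-positive notifications in six average areas are 6 × 2200/80 = 165 a year, so 250 Index cases are 250/165 = 1.5 years' worth.
- Wider comparator: 360/2200 = 16% of one year's smear-positive notifications in the city.

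The prevalent count is a cross-section, whereas the 360 accrue over time. Counting cases that arise during recruitment, or sources outside the six areas, would lower f.

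**3. From true share to observed match.** Let R be the true share of neighbourhood TB due to recent transmission. Let k be the number of other chain members who could give a match, each sequenced with probability f. Then observed match = R × [1 − (1 − f)^k]. Independence and the values of k are assumptions.

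| k | chance of a link, f = 0.31 to 0.40 | observed match if R = 80% | R implied by an observed 30% |
|---|---|---|---|
| 1 (direct source only) | 31% to 40% | 25% to 32% | 97% to 75% |
| 2 | 52% to 64% | 42% to 51% | 57% to 47% |
| 4 | 77% to 87% | 62% to 70% | 39% to 34% |

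The observed match falls short of R in every row. How far depends strongly on k, which the documents do not give. An observed 30% is compatible with a true share anywhere from about 34% to 97% over this grid.

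**The case against.** The strongest reply is that this is illustrative Discussion text, introduced as an example and phrased tentatively. No analysis in Methods classifies a non-match as reactivation. That stands: a reader might infer that the plan contains a rule turning low match into reactivation, and it does not. What remains is that reactivation is the only explanation offered.

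Second, Methods already compares all pairs, including pairs from different neighbourhoods and by travel time, and asks about shared venues such as workplaces. This also stands. The plan is not confined to each neighbour's own Index case. But the genomic comparisons need an isolate from both ends of a link, and the venue data are not tied to the low-match reading.

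Third, the Discussion acknowledges that the proportion of cases included matters. It does, but it then treats only COVID-19 shortfalls. Full recruitment would still leave sources outside the sequenced set.

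Fourth, the size is uncertain. The 31-40% counts direct sources only and assumes equal catchments, and coverage of notified CHC cases may be high. A reader might infer that almost no neighbour could match the own Index case. That needs sources spread at random, whereas the Introduction reports self-reported incidence of 675 per 100,000 a year in neighbouring households against 325 in randomly selected neighbourhoods. Nor is the 30% under 'Genomic relatedness' a cut-off for a low match. It is a power scenario, set beside about 60% for households and at most 10% for the community.

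Finally, the text does not claim that SNP distance alone shows direction. The sentence is conditional, and genomic and network analyses are named together.

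**Conclusion.** The point holds as a matter of interpretation. A low neighbourhood match cannot alone separate reactivation from recent community transmission, and incomplete sequencing biases the reading towards reactivation. The direction of the bias needs only that some sources go unsequenced, which the recruitment design makes certain in practice.

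Its size is not fixed by the documents. With equal catchments, a randomly drawn direct source in the six areas has roughly a 31-40% chance of being sequenced. The match rate can be higher because other chain members also count. The documents do not support treating 31-40% as a ceiling, and no stated sample-size or power figure is wrong. The change is worth making because the inference bears directly on the decision that the study is meant to inform.

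**What to change.** - In the Discussion, describe a non-match as not linked to a sampled case, and name recent transmission from unsampled sources beside reactivation as an explanation of a low match.
- From the all-pairs data already planned, report the share of neighbourhood isolates within the chosen SNP threshold of any sequenced isolate. Present it as a minimum for recent transmission, on the assumption that the threshold is tight enough for a match to mean a recent link.
- Beside it, give the estimated sampling fraction (sequenced cases over notified cases, and over expected prevalent cases, in the six areas) and a sensitivity range over plausible sampling fractions and chain sizes, as in the table above.
- Do not infer spread from Index households to neighbours from SNP distance alone. Leave direction open unless other evidence, such as symptom-onset dates, supports it.

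The cost is a change of wording and one calculation on isolates already collected. No extra recruitment or sequencing is needed. The downside is a weaker conclusion about reactivation.
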